## Methods and design

### Setting

The Capital Region of Denmark has a population of 1.6 million people. Patients in the Capital Region of Denmark are referred by their general practitioner (GP) or other treatment providers to a central diagnostic and referral centre within the mental health services that yearly assesses 20.000 referrals. About 4000 patients are further evaluated in person and diagnosed by the centre.

Five mental health centres in the region provide treatment packages for first-episode depression and will include participants in the study. The Mental Health Centre Amager and the Copenhagen centre consisting of two clinics located in the City of Copenhagen and treat approximately half of all patients, whereas Ballerup and Glostrup treat approximately a third of patients in the surrounding suburb (Sup. Figure 2). The Psychiatric Centre Northern Zealand treats approximately 16% of patients and is located north of Copenhagen, in a region of intermediate urbanisation with individual municipalities classified as rural.

### Study population

We aim to establish a cohort of 800 patients referred to the Danish treatment packages for unipolar first-episode, non-psychotic depression during 2021–2025. We recruit patients from all six clinics in the region. Each clinic receives approximately 100–250 treatment referrals yearly, and approximately 1100 patients are referred yearly. Approximately 80% of referrals are sent directly to the clinics. Patients are recruited during evaluation at the central diagnostic and referral centre or the first consultation in the clinics. Approximately 88% of referrals result in treatment package initiation.

During 2019–2020, 37% of patients were on an antidepressant (usually the selective serotonin reuptake inhibitor (SSRI) Sertraline from their GP) when starting the treatment package, and 54% of patients ended the treatment package on an antidepressant medication. 13% of patients were transferred to a treatment package for a different primary diagnosis group, e.g., generalised, social anxiety, post-traumatic stress disorder, emotionally unstable personality, avoidant personality disorder, eating disorder or obsessive–compulsive disorder. 20% dropped out of treatment. 5% of patients were hospitalised during their treatment package; hospitalization does not preclude the continuation of the treatment package.

The treatment package is a program with manualised psychotherapy in groups of eight patients as the core treatment module together with psychoeducation for the patient and relative (Sup. Table 1). In brief, a treatment package consists of 15–18 h: 2–3 h of initial workup followed by 6 h of individual therapy or 12 sessions of 2 h group therapy (8 patients per group); 1–2 h of engagement and psychoeducation of relatives; 1–5 h of medication clinic; and 2 h of relapse prevention. The program is designed around group-based CBT, but clinics also offer alternatives to CBT, e.g., psychodynamic and schema therapy, and groups for specific demographics, e.g., men or adolescents, and individual therapy. Medication is available as needed.

The research and assessment at baseline for recruited participants is conducted at the Neurobiology Research Unit (NRU) at the Copenhagen University Hospital Rigshospitalet and followed by clinicians from the Mental Health Centre Copenhagen who are not involved in the patient's treatment.

### Inclusion and exclusion criteria for patients

Patients between 18 and 65 years of age referred to a treatment package for single-episode depression will be recruited (Table 1) with minimal exclusion criteria to recruit representative adult outpatients who would typically receive treatment in routine practice (Table 1), of which the majority are women (71%) and aged 18–35 (68%) (S. Figure 1). Patients over 65 (approximately 0.7% of the target population) are excluded because of potential age-related cognitive decline, concomitant medical conditions, or medications that could interact with assessments or treatment (S. Figure 1). Allocation into the subcohorts is based on eligibility, e.g., MRI compatibility, scheduling, and patient willingness to participate.

**Table 1 Tab1:** Inclusion and exclusion criteria for patients

Patient inclusion criteria:
• Fulfilment of ICD-10 diagnostic criteria for a primary depressive episode (i.e., not secondary to known organic or other psychiatric disorder) • Referral to a treatment package for single-episode depression • Age between 18 and 65 years
**Exclusion criteria:**
• Psychosis or psychotic symptoms • History of severe head trauma involving hospitalization or unconsciousness for more than 5 min • Known, substantial structural brain abnormalities • Insufficient Danish language skills to complete questionnaires and cognitive testing
**Additional exclusion criteria for subcohort I:**
• Severe somatic disease • Contraindications for MRI (e.g., metal implants, claustrophobia, or back problems)
**Additional exclusion criteria for subcohort I:**
• Use of psychotropic drugs • Exposure to radioactivity > 10 mSv within the last year • Pregnancy or breastfeeding

The primary depressive episode, consistent with the International Statistical Classification of Diseases and Related Health Problems version 10 (ICD-10) criteria for MDD without psychotic features (F32.1, F32.2, F32.8 and F32.9), is confirmed by a specialist in psychiatry at the central diagnostic and referral centre.

### Inclusion and exclusion criteria for healthy controls

Data from HCs for comparisons to patients with MDD are available on-site from recent and concurrent projects, stored in the Cimbi database described in [32] including the BrainDrugs-Epilepsy study [33]. Apart from psychiatry-related issues (e.g., no current or history of mental illness or unstable somatic condition), the HC meet the same inclusion and exclusion criteria as required for patients.

### Data collection

The patients will undergo a multi-modal investigative program at inclusion and will be followed up after treatment and 12 and 18 months after treatment initiation with questionnaires assessing clinical status (Figs. 1 and 2). Apart from follow-up measures and information extracted from patient files and Danish health and social registries, all data collection will occur before the patient starts treatment.

**Fig. 2 Fig2:**
[figure not shown]
Flow diagram (STROBE) of the BrainDrugs-D cohort study. CVD: (Center for Visitation og Diagnostik) the central referral center within the mental health services in the capital region of Denmark, QIDS-SR: Quick Inventory of Depressive Symptomatology – Self Report, BSI-18: 10 item Brief Symptom Inventory, SCL-10: 10 item Symptom Checklist, mSDS: Modified Sheehan Disability Score, WHO-5: World Health Organisation—Five Well-Being Index (WHO-5), NEQ: Negative Effects Questionnaire, PRISE: Patient-Related Inventory of Side Effects

#### Baseline

##### Questionnaires

Questionnaires will be completed through a secure, web-based survey system hosted by the research centre so that participants can complete questionnaires electronically, either at home or during their visit to the research centre. Online questionnaires are sent via a national secure mail platform used by citizens in regular correspondence with public institutions and the health care system.

Measures include several salient domains in the clinical characterisation of the patient, among others, assessments of demographics (e.g., ethnicity, education, and marital status); medical and psychiatric history; depressive symptoms and impact of depression behaviour and day-to-day life; treatment preferences and expectations, life experiences; and a broad range of state and trait psychometrics. Some questionnaires will only be given to patients in subcohorts I-II (Table 2).

**Table 2 Tab2:** Questionaries Additional questionnaires for the subcohort I-II only are in bold

Symptom profile and Severity	Cognitive style	Upbringing and life history	Functioning and quality of life
Inventory of Depressive Symptomatology – self-report (IDS-SR) [34]	Mentalisation Questionnaire (MZQ) [35]	Online Stimulant and Family History Assessment Module (OS-FHAM) [11]	Cognitive Complaints in Bipolar Disorder Rating Assessment (COBRA) [36]
Dimension of Anger Reactions (DAR-5) [37]	Ruminative Response Scale (RRS) [38]	Child abuse and trauma scale (CATS) [39]	Modified Sheehan Disability Score (mSDS)
Generalised Anxiety Disorder 7-item (GAD-7) [40]	Perth Alexithymia Questionnaire (PAQ) [41]	**Parental Bonding Instrument (PBI)** [42]	WHO 5 wellbeing index (WHO-5)
Cohen's Perceived Stress Scale (PSS) [43]	**Mindful Attention Awareness Scale (MAAS)** [44]	**Stressful Life Events (SLE)** [45]	Changes in Sexual Functioning Questionnaire (CSFQ) [46]
Brief Symptom Inventory (BSI) [47]	**Short form of Metacognitions Questionnaire (MCQ-30)** [48]		Questions from the Copenhagen Aging and Midlife Biobank (CAMB) [49]
Symptom checklist (SCL-10) [50]	**Coping Self-Efficacy Scale (CSES)** [51]		Revised Sociosexual Orientation Inventory (SOI-R) [52]
Snaith-Hamilton Pleasure Scale (SHAPS) [53]			
**Pittsburgh Sleep Quality Index (PSQI)** [54]			

##### Medical records and registry data

Detailed medical information about previous illness, medication usage, hereditary dispositions, drug, tobacco, and alcohol intake will be acquired for all participants through interviews, self-report questionnaires, electronic medical records (EMR), and registry data.

Data extracted from the EMR will include treatment codes from the MDD treatment package, dates for treatment package start and completion, psychiatric comorbidities; and standard clinical blood work (e.g., HBA1c, TSH, CRP, and cholesterol). In addition, hormonal contraceptive and psychotropic medication prescription and usage (from 1995 onward) will be extracted from the Danish National Prescription Registry [55, 56]. This information includes prescribed medication and dosage and when the patient redeems a prescription. We will retrieve information on lifetime comorbidity from The Danish National Patient Registry (DNPR) [57]. From the Medical Birth Registry, we will obtain data on maternal and maternal perinatal health [58]. We will also collect information on alcohol and drug abuse treatment from the National Registry of Alcohol Treatment and Registry of Drug Abusers Undergoing Treatment. From the social registers in Statistics Denmark, we add data on marital status, occupational history, ethnicity, and educational level [59].

##### Cognitive testing

All patients are assessed with a ~ 1-h neuropsychological test battery, including ‘cold’ (emotion-independent) cognitive tasks indexing reaction time; psychomotor speed; verbal learning and memory; working memory; and executive functions, as well as ‘hot’ (emotion-dependent) cognitive tasks from the Danish version of the EMOTICOM test-battery indexing emotion recognition; emotion detection; and moral emotions in social situations [60].

Patients in subcohorts I-II will complete an additional ~ 1 h of testing with tasks assessing mental flexibility, verbal fluency, and visuospatial learning and memory (see Additional questionnaires for the subcohort I-II only are in bold.

Table 3 for a complete overview of all cognitive tasks). In addition, patients’ subjective experiences of cognitive disturbances will be assessed by the Cognitive Complaints in Bipolar Disorder Rating Assessment (COBRA) questionnaire [36].

**Table 3 Tab3:** Cognitive testing before treatment

Cognitive Test	Cognitive Domaine
**Whole Cohort**	
Simple Reaction Time task (SRT)	Reaction time
Trail Making Test A & B	Psychomotor speed/executive function
Symbol Digit Modality Task (SDMT)	Psychomotor speed/working memory
Letter-Number Sequence (LNS)	Working memory
D-KEFS Color-Word Interference Test (Stroop)	Executive function
Rey Auditory Verbal Learning Test (RAVLT)	Learning/memory
EMOTICOM Emotional Recognition Task (ERT)	Emotion recognition accuracy
EMOTICOM Emotional Intensity Morphing Task (IMT)	Emotion perceptual detection threshold
EMOITCOM Moral Emotions Task (MET)	Social cognition: guilt and shame
**Additional testing in the subcohorts**	
D-KEFS Verbal Fluency	Executive function
Rey Complex Figure Test (RCFT)	Visuo-spatial learning/memory
Probabilistic Reversal Learning task	Learning within a feedback context
Screen for Cognitive Impairments in Psychiatry—Depression (SCIP-D)	Memory, working memory, vocabulary, psychomotor speed

Patients in subcohorts I-II will complete an additional ~ 1 h of testing with tasks assessing mental flexibility, verbal fluency, and visuospatial learning and memory (see Additional questionnaires for the subcohort I-II only are in bold.

##### Blood biochemistry, genetics, and gene expression

Venous blood samples will be collected for serum, plasma, DNA, and RNA extraction. Identifying biomarkers relevant to the course of depression is an area of research that is evolving rapidly. Thus, based on an ongoing critical literature review, the search for and analysis of specific biomarkers may change during the study period. Currently, the blood biomarkers include inflammation parameters (e.g., high sensitivity CRP) [61, 62] and neurotrophic factors (e.g., BDNF and S100B) [63, 64].

DNA from blood samples will be used for microarray-based genotyping of MDD candidate genes, genes of relevance for MDD (e.g., rs41271330, 5-HTTLPR, COMT, and BDNFval66met), drug metabolism (e.g., CYP2D6, CYP2C19, UGT1A1, ABCB1, ABCC1) and to compute polygenic risk scores in all participants after genome-wide genotyping in the future. DNA will also be used for epigenetic analysis, and circular extrachromosomal DNA, a form of decomposed free DNA [65], will be extracted and characterised. RNA will be extracted for gene transcription profiles using microarray or TAG-based methods (mRNA and microRNA).

DNA from blood samples will be used for microarray-based genotyping of MDD candidate genes, genes of relevance for MDD (e.g., rs41271330, 5-HTTLPR, COMT, and BDNFval66met), drug metabolism (e.g., CYP2D6, CYP2C19, UGT1A1, ABCB1, ABCC1) and to compute polygenic risk scores in all participants after genome-wide genotyping in the future. DNA will also be used for epigenetic analysis, and circular extrachromosomal DNA, a form of decomposed free DNA [65], will be extracted and characterised. RNA will be extracted for gene transcription profiles using microarray or TAG-based methods (mRNA and microRNA).

Gene analyses will be based on a priori models of genetic variations known to modulate pharmacotherapy and psychotherapy responses. The results will be used to calculate a polygenic risk score for diagnosis and treatment response and meta-analyses with established polygenic risk scores for MDD and those currently developed for anxiety and anxiety disorders, including treatment response [66].

##### Electroencephalogram

In subcohort I, we will record resting state EEG and event-related potentials (ERPs) with simultaneous two-lead electrocardiography (ECG) to measure autonomic nervous system activation. EEG will be recorded using a 256-channel HydroCel Sensor Net system (MagstimEGI, USA) at 1000 Hz, where the vertex electrode serves as the reference. Impedances across all electrodes will be kept below 50 kΩ. ECG will be acquired at 1000 Hz using a Physio 16 device (MagstimEGI, USA). EEG/ERP recording: resting EEG (6 min eyes closed and eyes open), two-tone auditory oddball and the LDAEP tasks.

##### MRI

Participants in subcohort I will undergo MRI using a Siemens 3-Tesla Magnetom Prisma scanner. High-resolution structural T1-, T2-, and diffusion-weighted MR images will be acquired as well as ultra-fast functional magnetic resonance encephalography (MREG) asses cardiovascular brain pulsations [67]. Resting-state and task-based blood oxygen level-dependent (BOLD) fMRI scans will be acquired to measure related brain function. To assess distributed and intrinsic brain functional connectivity patterns, we will acquire a resting-state fMRI scan (10 min), during which participants are asked to close their eyes, let their minds wander and not fall asleep. Participants will complete established tasks to assess processes involved in cognition and mood, e.g., the Cyberball task, a ball-tossing game during which the participant interacts with fictitious characters to simulate experiences of social inclusion, exclusion, rejection and ostracism [68]. Trained research personnel will instruct participants on how to perform all tasks.

##### PET imaging

Participants in subcohort II will undergo PET neuroimaging with [^11^C]-UCB-J, which binds to the presynaptic vesicle glycoprotein 2A (SV2A). SV2A is ubiquitously and homogeneously located in synapses across the brain and allows for the determination of SV2A binding and presynaptic density in the brain [69, 70]. However, due to the ubiquitous distribution of SV2A, there is no proper reference region in the brain, and we, therefore, measure the arterial input function. PET scanning is conducted using a High-Resolution Research Tomography (HRRT) PET scanner (CTI/Siemens, Knoxville, TN, USA). First a 6 min transmission scan, then an intravenous bolus of < 400 MBq of [^11^C]-UCB-J administered over 20 s followed by a 90-min dynamic acquisition (256 × 256 × 207 voxels; 1.22 × 1.22 × 1.22 mm).

#### Treatment and life events

As the study is observational, we will not interfere with or delay treatment. EMR and registry data during treatment and until the 18 months from inclusion will be extracted to inform the individual treatment path, i.e., what treatment the individual patient received, e.g., amount of individual psychotherapy sessions and when, timing, type and dose of medication and switches, and participation in group therapy. Using registry data, we can also follow life events, e.g., change of residence, divorce, and employment.

#### Follow-up

Patient-reported outcome measures assessing depression symptom severity and clinical status are sent via the national secure mail platform at three time points: 6, 12 and 18 months after treatment start (Table 4). Complete registry follow-up is done at 18 months as well.

**Table 4 Tab4:** Follow-up Measurements ^a^Omitted if the patient did not receive antidepressant medication

Measures	6 months	12 months	18 months
Quick Inventory of Depressive Symptomatology (QIDS-SR)	X	X	X
BSI-18, SCL-10, WHO-5 and mSDS	X	X	X
Patient-Reported Inventory of Side-Effects (PRISE)[51]^a^	X	X	X
Negative Effects Questionnaire (NEQ)	X		

##### Primary and secondary outcome measures

The primary clinical outcomes are categorical: *improvement* defined as ≥ 50% reduction in QIDS and *remission* after the treatment package defined as a QIDS ≤ 5. The secondary outcome is *change* in depression severity as measured by QIDS.

##### Tertiary outcome measures

The ten-item depression and anxiety symptom checklist (SCL-10) [50, 71], well-being measured by WHO-5 [50, 72], and disability measured by a modified Sheehan Disability Scale (mSDS) are the established treatment effect parameters by the Mental Health Services of the Capital Region of Denmark.

Tertiary endpoints are three measurements of psychosocial remission defined as a WHO-5 score of > 49, an SCL-10 score of < 26 and an mSDS score of < 10. Additional tertiary clinical endpoints are changes in wellness (WHO-5), disability (mSDS), and symptomatology on the Brief Symptom Inventory 18 (BSI-18) and the SCL-10.

Two questionnaires assessing the negative effects of psychological and antidepressant treatment will be sent at the first follow-up, at the end of the treatment package. We use the Patient-Reported Inventory of Side-Effects (PRISE), originally developed and validated in Danish and also used in the STAR*D trial [71, 73]. The questionnaire is omitted if the patient has not been or is not on antidepressant medication. We use the short 20-item form of the Negative Effects Questionnaire (NEQ) to assess adverse and unwanted events in psychological treatment, i.e., new symptoms, dependency, stigma, hopelessness, and the experienced quality of treatment [74, 75]. Both baseline characteristics and treatment experiences, e.g., negative effects on the NEQ, will be used to investigate reasons for CBT and treatment package drop-out.

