**Methods:**

All patients are examined before receiving a standardised treatment package for adults aged 18–65 with first-episode depression in six public outpatient clinics in the Capital Region of Denmark. From this population, we will recruit a cohort of 800 patients for whom we will acquire clinical, cognitive, psychometric, and biological data. A subgroup (subcohort I, *n* = 600) will additionally provide neuroimaging data, i.e., Magnetic Resonance Imaging, and Electroencephalogram, and a subgroup of patients from subcohort I unmedicated at inclusion (subcohort II, *n* = 60) will also undergo a brain Positron Emission Tomography with the [^11^C]-UCB-J tracer binding to the presynaptic glycoprotein-SV2A. Subcohort allocation is based on eligibility and willingness to participate. The treatment package typically lasts six months.

Depression severity is assessed with the Quick Inventory of Depressive Symptomatology (QIDS) at baseline, and 6, 12 and 18 months after treatment initiation.

The primary outcome is remission (QIDS ≤ 5) and clinical improvement (≥ 50% reduction in QIDS) after 6 months. Secondary endpoints include remission at 12 and 18 months and %-change in QIDS, 10-item Symptom Checklist, 5-item WHO Well-Being Index, and modified Disability Scale from baseline through follow-up. We also assess psychotherapy and medication side-effects.

We will use machine learning to determine a combination of characteristics that best predict treatment outcomes and statistical models to investigate the association between individual measures and clinical outcomes.

We will assess associations between patient characteristics, treatment choices, and clinical outcomes using path analysis, enabling us to estimate the effect of treatment choices and timing on the clinical outcome.

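### PRISE is taken only at follow-up and only in patients exposed to an antidepressant, so on its own it cannot tell complaints arising on medication from complaints present at entry or residual depression

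*Protocol article*

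**What the plan says.** The abstract states an aim for this measure: "We also assess psychotherapy and medication side-effects". Under Tertiary outcome measures the article writes "We use the Patient-Reported Inventory of Side-Effects (PRISE), originally developed and validated in Danish", and of PRISE and the NEQ together: "Two questionnaires assessing the negative effects of psychological and antidepressant treatment will be sent at the first follow-up". The same section restricts who answers PRISE: "The questionnaire is omitted if the patient has not been or is not on antidepressant medication". A footnote to Table 4 also leaves out patients who received no antidepressant.

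Table 4 (Follow-up) lists "Patient-Reported Inventory of Side-Effects (PRISE)[51]^a" with marks at 6, 12 and 18 months. Table 2 (Questionnaires, under Baseline) does not list PRISE. The Data collection section places everything except follow-up measures and record or registry extraction before the start of treatment.

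On exposure, Study population reports for clinic patients in 2019–2020 that "37% of patients were on an antidepressant" when starting the package and that "54% of patients ended the treatment package on an antidepressant medication". The recruitment target is in the same section: "We aim to establish a cohort of 800 patients".

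**The concern.** A side-effect inventory can be interpreted in two ways. One compares the patient with his or her own earlier state; the other compares medicated with unmedicated patients. The schedule provides neither for PRISE. Patients enter with depressive symptoms, and some are already medicated. A complaint ticked at 6 months may have begun on the drug, may have been there at entry, or may be depression that has not lifted.

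What is at stake is the meaning of the medication side-effect results. The Background names safety and tolerability as underexplored, so readers will want to use them. The gap lies in data collection, so an analysis plan written later cannot recover a baseline PRISE that was not taken.

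**Working it through.** No sample size, power or error rate is tied to PRISE, so there is no stated figure to reproduce. The check sets the schedule side by side and then sizes the groups concerned.

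**Schedule**

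| Measure | Baseline | Follow-up (Table 4) |
|---|---|---|
| PRISE | not in Table 2 | 6, 12, 18 months, exposed patients only |
| QIDS | yes (Abstract, Objectives) | 6, 12, 18 months |
| IDS-SR | yes (Table 2) | no |
| BSI / BSI-18 | BSI (Table 2) | BSI-18 at 6, 12, 18 months |
| SCL-10, WHO-5, mSDS | yes (Table 2) | 6, 12, 18 months |
| CSFQ | yes (Table 2) | no |
| PSQI | subcohorts I–II only (Table 2) | no |

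Prescription registry data give drug, dose and redemption dates (Medical records and registry data). They date the exposure, not the complaint.

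Depression severity and general symptom load are thus known at entry and at the time of PRISE. Sexual function is known at entry for everyone, and sleep for the subcohorts. A baseline covariate need not be repeated to be useful, so CSFQ can serve in adjustment. The article does not list the PRISE items, so the degree of overlap is an assumption drawn from what the other scales measure.

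**Size of the groups**

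Inputs: 37% on an antidepressant at the start, 54% at the end (both 2019–2020 clinic data), 800 patients. Assumption: these shares carry over to the cohort.

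- On an antidepressant at the start: 0.37 × 800 = 296. Not on one: 800 − 296 = 504.
- On one at the end: 0.54 × 800 = 432.

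The overlap between start and end is not given, so only bounds are possible. Taking PRISE-eligible to mean exposed at any time:

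- All 296 stay on the drug and nobody else was exposed and stopped: 432 exposed; medicated before the package 296/432 = 69%; later starters 432 − 296 = 136.
- None of the 296 is still on it at the end: at least 296 + 432 = 728 exposed; medicated before the package 296/728 = 41%; later starters 432.
- Everyone is exposed at some time: 296/800 = 37%; later starters 504.

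So roughly 37% to 69% of patients answering PRISE would have been medicated before the package. The others, between 136 and 504, could have given a drug-free PRISE at entry, and the schedule does not take one. In the first case 800 − 432 = 368 patients are never exposed and receive no PRISE at all; in the third case there are none.

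**What a baseline PRISE would and would not do**

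- Not on an antidepressant at entry: the baseline is drug-free, and complaints that are new or worse can be called treatment-emergent.
- Already on one: the baseline is on-drug. It separates complaints present before the package from later ones, but not drug from depression. A persisting complaint may be a real side effect.

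**The case against.** The strongest reply is that the article states no harm. It gives no rule for scoring, counting or attributing PRISE answers, and says under Statistical analyses that more specific plans will be published. A reader might infer that every complaint will be counted as a medication side effect, but nothing in the text says so. Whether the form itself asks patients to attribute complaints to their medicine cannot be seen from the article. This limits the point to what PRISE alone can distinguish. It does not remove the point, because the schedule is tabulated at both ends.

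A reader might also infer that patients who do not remit will appear to tolerate medication worse. The direction is plausible, but the article states no analysis of PRISE against remission and gives no complaint rates from which a size could be worked out. The drop-out analysis names the NEQ as its example.

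Third, the 37% can be made to carry too much. It describes clinic patients in 2019–2020, and it marks the group in whom a baseline PRISE helps least. The gain is clearest in those not medicated at entry.

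Fourth, the existing scales and prescription dates allow adjustment. That stands, but as partial adjustment: they are not the same items, and they do not date the onset of a complaint.

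Finally, PRISE enters none of the numbered hypotheses and is not among the endpoints that the tertiary section names. This stands and limits the weight of the point.

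**Conclusion.** The point holds as a limitation of the measurement schedule. PRISE has no baseline and no unmedicated comparison, so by itself it cannot distinguish complaints arising on medication from those present at entry or from residual depressive symptoms. Partial adjustment is possible with data already planned. The documents do not support a statement that side-effect rates will be inflated, or by how much.

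The size is given as numbers of patients, not as bias: about 296 of 800 medicated at entry and between 136 and 504 later starters without a drug-free PRISE. This rests on the 2019–2020 shares carrying over and on counting anyone ever exposed as eligible. The point is a low-severity, inexpensive improvement and does not touch the primary or secondary hypotheses.

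**What to change.** 1. Add PRISE to the baseline electronic questionnaires for all patients still to be enrolled, whatever their medication status.
2. In patients not on an antidepressant at entry, report treatment-emergent complaints: new, or worse than at baseline.
3. In patients already on one, report separately and describe change only as new since package start. Do not treat persisting complaints as excluded side effects, because the baseline is on-drug.
4. For patients already enrolled, adjust follow-up PRISE for the overlapping baseline measures (IDS-SR, BSI, CSFQ) and for concurrent QIDS-SR and BSI-18, use prescription dates to classify exposure, and label the rates as complaints on medication rather than side effects.
5. While editing, reconcile the PRISE time points: the tertiary section speaks of the first follow-up, Table 4 marks all three.

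The cost is one more questionnaire in an existing web survey, with slightly more burden at baseline and no added visit. The PRISE baseline will be incomplete across the cohort, so results from patients with and without it should be shown apart.
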